### 2.3.3 Study Methodology

2.3.3.1 Pre-recruitment

Participants will be invited to join the study via advertising in public media (newspapers, magazines, as appropriate), via posters in schools, pharmacies, GP surgeries, and through letters or telephone calls to families who have expressed an interest in joining further clinical investigations and are listed on a database held at the Medical Entomology Centre. A detailed Participant Information Booklet (PIB) will be provided to explain the purpose of the study. This will include a children’s section explaining what will happen if the person enters the study.

A member of the study team will conduct a brief interview to establish whether the person will be suitable for entry into the study. If the person wishes to enter the study, they will be conducted through a standardised consent procedure. Potential participants must have had access to the PIB for at least 24 hours before the recruitment takes place.

2.3.3.2 Recruitment (Day 0)

Screening:

Each potential participant will be asked for permission to assess their hair to confirm the presence of live head lice. The assessment will be made by dry combing the hair with a plastic fine-toothed head louse detection comb. Lice found during the assessment will not be removed. Other family members who give their verbal permission can also be assessed for the presence of living lice and may join the study provided they meet the inclusion/exclusion criteria.

Details will be recorded of how many people share the place of residence with the participant. Details will also be recorded of the number of people assessed and found to have lice, the number assessed and found not to have lice and the number that were not assessed. The number of people enrolled in the study will also be recorded.

Consent/Assent:

Participants and/or parents/guardians will be asked if they understand the requirements of the study and if they have any further questions concerning it. Provided they still wish to enter the study and meet the inclusion/exclusion criteria for entry, the participant or parent/guardian (when the participant is below the age of 16) will read and sign the Consent Form. The Investigator will countersign the Consent Form.

A separate Assent Form will be available for those under the age of 16 provided they are capable of signing their name. The Investigator and the parent/guardian will countersign the Assent Forms.

Children too young to provide signed assent may be enrolled on the basis of parental consent.

Case Record Form completion:

Personal data allowing identification of an individual will not be recorded in the CRF. However, as there are no source medical documents (i.e. patient medical records) available to the investigators a Source Data Verification Sheet will be completed for each participant that will be maintained separately from all other study documentation. This Sheet will include information such as name, date of birth, address, and contact details for the General Practitioner.

The following information will be recorded in the CRF:

1. **Declaration of Receipt of Informed Consent**: Confirmation that informed consent and assent (where relevant) was obtained, that a copy of the consent has been given to the participant and/or parent/guardian and that the original will be retained.
2. **Identification**: Participant's study number and age.
3. **Hair Characteristics**: Characteristics will be recorded of the participant’s hair:
   1. Length: closely cropped, above ears, ears to shoulders, below shoulders
   2. Thickness: fine, medium, thick
   3. Degree of curl: straight, wavy, slight curl, tight curl
   4. Type: dry, normal, greasy
4. **Head Lice Details**: When the participant was last treated for head lice (an exact date if treated within the previous four weeks), the treatment that was used and the outcome (success or failure). The severity of the current louse infestation will be assessed using the following scale:
   1. Light infestation: single louse found only after 5-6 combs of the hair
   2. Moderate infestation: single louse found on the first comb of the hair
   3. Heavy infestation: more than one louse found on the first comb of the hair
5. **Medication Current at Entry**: Any medication being taken along with the date the medication started the total dose and the reason for the medication.
6. **Medical History**: Medical history and any current illnesses will be recorded.
7. **Inclusion/Exclusion Criteria**: Confirmation that the participant meets the inclusion/exclusion criteria for entry into the study.

Randomisation:

The Investigator will carry a block of sequential numbered envelopes, which correspond to the randomisation numbers on the CRFs. Each envelope will contain a randomised treatment allocation. After consent has been received, the next sequential numbered envelope will be opened and the specified treatment allocated.

Treatment:

A member of the study team will apply the treatment to the participant and the participant number and participant initials will be added to the label of the bottle used. Any unused product will be retained and returned to so that the weight can be recorded and the amount of product used calculated.

The products will be applied in the following way:

**KindaPed AF (5% 1,2-octanediol alcohol free lotion) 2-2.5 hours** will be applied directly to dry hair. Sufficient product will be applied to wet all the hair and scalp. More than one bottle can be used if required. The product will be left in place for 2 hours, however for practical purposes and convenience of the participants a small flexibility has been included in the treatment time so that the product may remain on the hair for up to 2.5 hours. The product will then be washed off using non-medicated shampoo. The hair will then be rinsed with water. Hair can be dried in the usual way following hair washing after treatment.

**KindaPed AF (5% 1,2-octanediol alcohol free lotion) 8 hours or overnight** will be applied directly to dry hair. Sufficient product will be applied to wet all the hair and scalp. More than one bottle can be used if required. The product will be left in place for at least 8 hours, if applied early enough during the day, but if applied late it will be left on overnight. The product will then be washed off using non-medicated shampoo. The hair will then be rinsed with water. Hair can be dried in the usual way following hair washing after treatment.

**KindaPed lotion (5% 1,2-octanediol with 20% alcohol)** will be applied directly to dry hair. Sufficient product will be applied to wet all the hair and scalp. More than one bottle can be used if required. The product will be left in place for 2 hours, however for practical purposes and convenience of the participants as small flexibility has been included in the treatment time so that the product may remain on the hair for up to 2.5 hours. The product will then be washed off using non-medicated shampoo. The hair will then be rinsed with water. Hair can be dried in the usual way following hair washing after treatment.

In all cases the participants will be reminded that a second treatment will be applied on Day 7.

Any household members who have lice but are unable to participate in the study for any reason will be offered a standard of care treatment (Hedrin 4% liquid gel) in order to reduce the risk of reinfestation of participants during the course of the study.

2.3.3.3 Follow up Assessments (Days 1, 6 and 9)

Assessments will take place on Days 1, 6, and 9 (+/- 1 day) – see section 2.3.3.5 for Day 14. At assessments, the participant’s hair will be combed with a head louse detection comb, and any lice found will be taped (with clear cellulose tape) into the participant’s CRF. In order to provide blinding and to minimise bias the study team member that conducts the follow up assessments will be different from the team member that applied the treatment at Day 0 and 7.

All adverse events and changes in concomitant medication will be recorded in the CRF.

- - - 1. Follow up Treatment (Day 7)

Treatment will be reapplied at Day 7 following the same procedure as at Day 0 (see section 2.3.3.2).

- - - 1. Final Assessment (Day 14)

The final assessment will take place 14 days (+/- 1 day) after the first treatment (the 15^th^ day of the study). The participant’s hair will be combed with a head louse detection comb and any lice found will be taped (with clear tape) into the participant’s CRF.

Participants who still have live lice at the end of the study will be offered a standard of care treatment (Hedrin 4% liquid gel).

All adverse events and changes in concomitant medication will be recorded in the CRF.

At the Day 14 assessment, the participant and/or parent/guardian will be asked to complete a questionnaire on the treatment that was applied at Day 0. This will include questions on how the participant’s scalp felt, how the hair felt, how easily the product washed out, and how convenient the participant and/or parent/guardian considered this treatment application time.

The Completion/Withdrawal Form will then be completed.

**2.3.3.6 Assessment Analysis**

Any lice found during the course of the study will be examined under the microscope to establish the sex and/or stage of development of the insects. It is expected that few adult lice will be found during the monitoring period. The presence of small lice (nymphs) will be evidence that not all of the eggs were killed by the first treatment and will be used as a measure of ovicidal activity. Continued monitoring enables the investigation to determine whether the presence of any lice is due to surviving lice or surviving eggs from which nymphs emerge. The occasional adult louse (1 or 2 only) found after the initial infestation is cleared would be indicative of re-infection (see section 3.1.2).

### 2.3.4 Concomitant Medication

The participant should not use any other form of pediculicide treatment while taking part in the study. If the use of such treatment occurs, the participant will be withdrawn from the study.

Other medication can be prescribed in the normal way although participants requiring Co-Trimoxazole or Trimethoprim should be withdrawn from the study.

All concomitant medicines should be listed in the CRF and any changes to such medicines, during the course of the study, recorded.

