### 3.1.2 Efficacy

The primary endpoint is cure, indicated by no evidence of active head louse infestation following the second application of treatment, or cure followed by reinfestation, indicated by limited numbers of adult or stage 3 nymphs on Days 9 or 14, as set out in the following treatment outcome algorithm.

The secondary endpoints are to confirm whether the treatment inhibits louse eggs from hatching (as demonstrated by no stage 1 or 2 nymphs after the first treatment) and the safety and acceptability of the treatment regimen.

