**Treatment Outcome Algorithm**

This algorithm has been developed by Medical Entomology Centre and P. N. Lee Statistics and Computing Ltd in order to impose limits within which the outcomes of treatment and any lice recovered can be interpreted.

Cure:

No lice present on Day 9 and Day 14.

Re-infestation

The following must all apply:

- - - Lice must be present at Day 9 and/or Day 14.
    - Adult lice and/or stage 3 nymphs must not be present at Days 1, 2 or 6.
    - Stage 1 or 2 nymphs must not be present at Day 9 or Day 14.
    - If stage 3 nymphs are present at Day 9 there must be no stage 1 or 2 nymphs present at Day 6.
    - Stage 3 nymphs may be present at Day 9 or Day 14 although they must not exceed 2* in number.
    - Adult lice should not exceed 2* at either Day 9 or Day 14.

In addition, the following may apply:

- If adult lice are present at Day 9 Stage 1 and stage 2 nymphs may be present at Day 6.

* The number 2 is an interpretation of the limits of “occasional”.

Ovicidal Failure Only

Ovicidal failure is evidenced by the presence of stage 1 nymphs within 2 days of the second treatment administered on Day 7

For ovicidal failure only, specific lice must not be present at Day 9 or Day 14:

- - - At Day 9 there must be no adult lice and no stage 2 or stage 3 nymphs.
    - At Day 14 there must be no adult lice or stage 3 nymphs.

This is equivalent to requiring stage 1 nymphs only at Day 9 and/or stage 1 and/or stage 2 nymphs only at Day 14.

Licidal Failure Only

All other outcomes are licidal failures.

For licidal failure only, there must be no stage 1 nymphs at Day 9 and no stage 1 or stage 2 nymphs at Day 14, so as not to satisfy the condition for ovicidal failure.

Licidal and Ovicidal Failure

Any subject not falling into groups 1, 2, 3 or 4, including those with missing values for the data necessary to make the classification into groups 1-4. This includes any subjects with missing data at days 9 or 14, as well as those subjects with evidence of lice at days 9 or 14, but missing data at days 2 or 6.

.

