## 3.2 Definition of Populations to be analysed

The Per-protocol Population:

Includes all participants treated according to the study protocol.

"Intention-to-treat" Population:

Includes all participants consenting and treated at least once. Premature terminations, due to treatment failure, adverse events etc., are included.

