## 3.4 Statistical Methods

Sample Size Determination:

The study has been designed to confirm that KindaPed AF (5% 1,2-octanediol alcohol free lotion) has an essentially similar efficacy comparable to that of KindaPed lotion (5% 1,2-octanediol with 20% alcohol). It is not designed as a full equivalence study but is designed to be able to identify any significant differences between the treatments in pair wise comparisons.

This study is based upon the same sample size as that used in four previous studies of head louse treatments conducted on behalf of Thornton & Ross Ltd (CTMK06, CTMK08, CTMK09, and CTMK10) for basic comparative purposes and is estimated to provide adequate data for demonstration of effect. The actual sample size of 40 per group makes allowance for dropout. Comparison of the results from this study can be made with the results from those studies with respect to similarities of population demographics, and with previous studies of 1,2-octandiol lotion (CTEP01 and CTEP02) with respect to efficacy outcome and acceptability.

Interim analysis

It is proposed to conduct an interim analysis of treatment outcome only after enrolment and completion of sixty (60) participants (approximately 20 in each group). This analysis will be conducted blind of treatment allocation using outcome data entered into a spreadsheet which would then be overlaid with treatment allocation identified only as “a”, “b”, or “c”. This will enable the Sponsor to identify whether one treatment is performing exceptionally well or exceptionally poorly and allow them to make a decision in good time whether they wish to extend or to curtail any aspect of the study. The results of this analysis will be conveyed to the Sponsor in narrative form only.

Analytical Methods:

The primary endpoint is the frequency of cure tested using the "intention-to-treat" population in comparison with the body of data obtained during previous studies using overnight or 2-2.5 hour application times for the product. Secondary endpoints will be the frequency of ovicidal failure and of reinfestation and the numbers of lice seen at the different assessment times. Other endpoints will be the safety of the product and participant acceptance.

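### Use of another pediculicide has no scoring rule: the same use leads to failure if disclosed before Day 14 and assessments then stop, but could count as success if first disclosed at Day 14

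*Protocol*

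**What the plan says.** Section 2.3.4 rules out any other pediculicide during the study and states: "If the use of such treatment occurs, the participant will be withdrawn from the study". It gives the consequence for participation but not for the outcome.

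The outcome is fixed in section 3.1.2. In the Treatment Outcome Algorithm, cure is "No lice present on Day 9 and Day 14". Re-infestation is defined by louse stage, number and day, with at most two adults at either late visit. The last class, licidal and ovicidal failure, takes everyone not placed elsewhere: "This includes any subjects with missing data at days 9 or 14". No class mentions other pediculicide use or withdrawal. The primary endpoint in section 3.1.2 is cure, "or cure followed by reinfestation, indicated by limited numbers of adult or stage 3 nymphs on Days 9 or 14", so re-infestation is also a success.

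Section 3.4 tests the primary endpoint in the intention-to-treat population. Section 3.2 puts everyone who consented and was treated at least once in that population, and adds: "Premature terminations, due to treatment failure, adverse events etc., are included". The per-protocol set is those treated according to the protocol.

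Concomitant medication is recorded at Days 1, 6, 9 and 14. The text for the Day 14 visit lists the combing first, the medication record later and the Completion/Withdrawal Form last.

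**The concern.** The withdrawal rule and the algorithm are not linked. Withdrawal affects the score only through the visits that go missing because of it. If use comes to light before Day 14 and assessments stop, a visit is missing and the participant is a failure. If it first comes to light at Day 14, both decisive combings may already exist, and the algorithm has nothing to set against them. The same conduct could then receive opposite primary outcomes, depending only on the visit at which it is admitted.

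The trial sets out to show that the alcohol-free product has lost no efficacy and to conclude essential similarity. Where a family turns to another product because the study product is failing, scoring the result as cure credits the study product with the other product's effect. In a trial looking for similarity, that kind of error can hide a difference.

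**Working it through.** The protocol states no figure on this point that could be reproduced. The sample size is carried over from earlier studies, and the argument does not rest on it. The check applies the algorithm to patterns of other pediculicide use.

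**Inputs.** Cure, re-infestation and failure classes and the missing-data rule: Treatment Outcome Algorithm. Re-infestation as success: section 3.1.2. Population: sections 3.2 and 3.4. Arm size of 40: section 3.4.

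**Assumptions the text does not state.** (a) Assessments stop at withdrawal. (b) A Day 14 combing already done is kept when use is disclosed at that visit. (c) Where the algorithm names Day 2, the Day 1 assessment is meant, since no Day 2 visit is scheduled.

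**Classification.**

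| Pattern | Disclosure | Class |
|---|---|---|
| Adults on Days 1 and 6, other product Day 7-8, clear on Days 9 and 14 | At Day 14 | Cure |
| Same | At Day 9, withdrawn, Day 14 missing | Licidal and ovicidal failure |
| Clear on Days 1 and 6, two adults on Day 9, other product Day 10, clear on Day 14 | At Day 14 | Re-infestation (success) |
| Same | At Day 12, withdrawn, Day 14 missing | Licidal and ovicidal failure |
| Clear through Day 9, other product Day 10, clear on Day 14 | At Day 14 | Cure |
| Clear on Days 1 and 6, five adults on Day 9, other product Day 10, clear on Day 14 | At Day 14 | Licidal failure |
| Clear on Days 1 and 6, stage 1 nymphs only on Day 9, other product Day 10, clear on Day 14 | At Day 14 | Ovicidal failure |

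Two comparisons without the other product show what can be concealed. In the first pattern, adults persisting on Days 9 and 14 would be a licidal failure. In the fifth, stage 2 nymphs at Day 14 would be an ovicidal failure.

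The last two rows mark the limit: lice on Day 9 outside the re-infestation pattern already decide the outcome. The score depends on the time of disclosure only when Day 9 is clear or fits that pattern.

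**Size.** The shift in an arm's success rate from k such participants is k/40:
- k = 1: 1/40 = 2.5 points
- k = 2: 2/40 = 5.0 points
- k = 3: 3/40 = 7.5 points
- k = 4: 4/40 = 10.0 points

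If the full randomisation list in section 2.3.2 were used (11 × 12 = 132, or 132/3 = 44 per arm), one participant would move an arm by 1/44 = 2.3 points. The documents give no basis for k.

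**The case against.** The strongest reply is that the protocol nowhere says use disclosed at Day 14 is scored as success. Section 2.3.4 ties withdrawal to use, not to disclosure, and the withdrawal form comes after the Day 14 medication record. One could read the text so that use triggers withdrawal, later combings are void, and the result is failure whenever disclosed. That reading is coherent, but voiding combings after use is not a stated rule, and the algorithm already assigns every participant a class without it. The reply does establish that late-disclosed use could be scored as success, not that it must be.

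The failure branch is also an assumption. Section 2.3.7 describes a participant withdrawn for non-compliance as still accessible to the investigator. If assessments continued, the asymmetry would shrink, but use disclosed early could then also be scored as cure.

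The window is narrow. Use before Day 9 matters only if withheld at Day 9 and then volunteered at Day 14. After a clear Day 9 there is little motive to use another product. A participant with one or two adults on Day 9 might have been classed as re-infestation anyway. These points stand and limit the likely frequency.

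The per-protocol analysis would probably exclude these participants and is a partial check, but it is not primary. A separate analysis plan could add a rule, but it would have to override an algorithm that this protocol fixes.

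A reader might infer that the standard-of-care product offered to infested household members outside the study will reach participants. The documents give its purpose as reducing re-infestation, and nothing in them indicates such diversion.

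**Conclusion.** The withdrawal rule in section 2.3.4 and the Treatment Outcome Algorithm need to be reconciled. As written, the score of a participant who used another pediculicide can turn on when the use is disclosed, and a failure followed by another product could be counted as a success in the primary intention-to-treat analysis. This rests on assumptions (a) and (b) and applies only when Day 9 is clear or fits the re-infestation pattern. If section 3.4, which names the frequency of cure and lists reinfestation as secondary, were taken to define the primary endpoint, the re-infestation route would fall away and the cure route would remain.

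The size is 2.5 points per participant in an arm of 40. The number of such participants is unknown. A reader might infer that the effect will favour the weaker arm and conceal a loss of efficacy of the alcohol-free product. The documents do not support that as a prediction: they give no cure rates, no rate of other pediculicide use and no evidence of a difference between arms. Where such use follows treatment failure, it would inflate that arm's cure rate and could mask a difference. This is a modest weakness, worth closing because it is easily closed.

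**What to change.** Add one scoring line to the Treatment Outcome Algorithm: a participant known to have used any pediculicide other than the allocated product after Day 0 and before the Day 14 combing is classed as a treatment failure in the primary intention-to-treat analysis, whatever the lice counts and whenever the use is disclosed. The same line excludes that participant from the per-protocol set.

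This scores the endpoint only and leaves the withdrawal rule and all clinical handling as they are. It uses the concomitant medication record already taken at each assessment. The question should not be moved ahead of the combing, because the answer could influence the assessor.

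The cost is one line of text and possibly slightly less favourable cure rates. Use that is never disclosed is not caught.
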